## Abstract

**Background:**

Smoking continues to be the leading preventable cause of death. Digital Interventions for Smoking Cessation (DISCs) are health communication programs accessible via the internet and smartphones and allow for greater reach and effectiveness of tobacco cessation programs. DISCs have led to increased 6-month cessation rates while also reaching vulnerable populations. Despite this, the impact of DISCs has been limited and new ways to increase access and effectiveness are needed.

**Objective:**

We are conducting a hybrid effectiveness-dissemination study. We aim to evaluate the effectiveness of a machine learning–based approach (recommender system) for computer-tailored health communication (CTHC) over a standard CTHC system based on quit rates and risk reduction. In addition, this study will assess the dissemination of providing access to a peer recruitment toolset on recruitment rate and variability of the sample.

**Methods:**

The Smoker-to-Smoker (S2S) study is a 6-month hybrid effectiveness dissemination trial conducted nationally among English-speaking, current smokers aged ≥18 years. All eligible participants will register for the DISC (Decide2quit) and be randomized to the recommender system CTHC or the standard CTHC, followed by allocation to a peer recruitment toolset group or control group. Primary outcomes will be 7-day point prevalence and risk reduction at the 6-month follow-up. Secondary outcomes include recruitment rate, website engagement, and patient-reported outcomes collected via the 6-month follow-up questionnaire. All primary analyses will be conducted on an intent-to-treat basis.

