#### Effectiveness Outcomes

##### Smoking Cessation: 7-Day Point Prevalence and Verification by Saliva Test NicAlert

The primary outcome measure will be 7-day point prevalence at the 6-month follow-up. The 7-day point prevalence will be assessed by asking, “Do you currently smoke cigarettes (smoked even 1 puff in the last 7 days)?” [33] The 7-day window provides an appropriate stringent measure to account for a cross-sectional snapshot. In a cessation trial, biochemical verification is used to monitor for differential misclassification by the randomization group. The degree of misclassification is moderated by characteristics of the smoking cessation intervention [34]. Studies that are in-person and intense generally have more misclassification because of the personal connection between the smoker and the counselor and therefore require biochemical verification. Less misclassification occurs in low intensity, light-touch studies. Further, differential misclassification increases with intervention differences between two groups. Since our intervention and control are both texting interventions, the potential for differential misclassification is reduced. Further, requiring biochemical verification can, in fact, lead to additional issues, including refusal to participate, thus biasing the sample [34,35]. However, based on peer review, we are conducting biochemical verification. To reduce the potential for biasing the sample due to the need for biochemical verification, we are using an opt-in procedure to conduct biochemical verification among those who indicated they had quit smoking at 6 months. If a participant indicates they have quit smoking at 6 months, they are contacted by the research study staff to see if they would like to opt-in to the biochemical verification. If a participant opts in, they will be mailed the NicAlert test strips (Nymox Corporation, St Laurent, Quebec, Canada) within 24 hours with clear instructions on how to take a picture and return the picture of the results to us electronically. NicAlert is a semiquantitative method that uses a dipstick to measure the level of cotinine in a sample of saliva. The test strip displays the result in seven zones. Each zone represents a range of levels of cotinine/smoking (eg, zone 0: 0-10 ng/mL, a nonsmoker, zone 6: >1000 ng/mL, a heavy smoker). The results will be read as 0-6, and as recommended, any value ≥ 1 will be considered as tobacco use [36-38]. Our staff will also be available by phone to help the smokers complete testing. Participants sending back the sample will receive an additional US $50 incentive (as outlined in the consent form) for completing biochemical verification.

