### Sample Size

#### Hypothesis 1: Dissemination

Our previous work [26,27] showed that having access to peer recruitment increased the proportion of African Americans to 23%, compared to 11% in the initial seeds (those recruited by advertisements). Using 10% as the base rate in the nonpeer recruitment group (no access to peer recruitment), we estimated sample size requirements by varying the proportion in the peer recruitment from 16% to 20%. With these assumptions, for our primary aim, we will need 219 smokers in each group to detect a difference of 10% (power=80%, α=.05). If we reduce the difference to 8% and 6%, we will need 319 and 525 participants in each group, respectively. Given that we will work with our panel to encourage recruitment of African American smokers in the peer recruitment group and may see bigger differences than those in our pilot study, we will have adequate power, particularly with the proposed sample size of 600 in each recruitment method. For recruitment time, previous trials estimated that the mean number of days to recruit a sample of 700 smokers was 244 (SD 81) days [27,40]. Assuming that peer recruitment proceeds with the same rate and SD, we can detect a difference in recruitment time as low as 14 days. Since we expect the comparison rate to be much slower, we are adequately powered to detect differences with a sample of 600 (power=80%).

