### Statistical Analyses

All primary analyses will be conducted on an intent-to-treat basis. Secondary analyses will explore dose-response effects among those with variable levels of adherence to the intervention. All analyses will be two-sided, and the alpha error will be set at .05. We will begin our analysis by examining univariate statistics (means, medians, SDs, and 95% CIs) and distributions. We will examine the balance of participant characteristics by study groups and account for any imbalances in our multivariable analysis. As appropriate, differences in measured characteristics (ie, demographics and prebaseline smoking behaviors) by group will be tested using Chi-square tests of independence (categorical variables), analysis of variance (continuous variables), or the equivalent nonparametric tests, depending on the distribution of the variables. Differences in baseline characteristics of the intervention and comparison groups will be assessed.

To test Hypothesis 1, we will categorize the smokers as either African Americans or not, and then use the chi-square statistic to test for differences between the peer recruitment and standard groups. We will also compare mean recruitment time between the two types of recruitment method using a *t* test. We will explore possible factors that may not be balanced between the smokers recruited from the two methods. If we find any significant differences, we will develop a linear regression model to further adjust for the influence of the confounders on the time to recruitment outcome. Within the peer recruitment groups, we will conduct a secondary analysis examining differences in demographic characteristic between peer recruited and directly recruited smokers. Using data provided by search engine advertisement managers, we will evaluate the performance of our online advertisements (number of users registered on Decide2Quit following an advertisement on the search engine).

To test Hypothesis 2, we will use a generalized linear model, which includes indicators of peer recruitment and recommender CTHC and the interaction between the two indicators as independent variables.

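### The abstract makes risk reduction a second primary outcome and the outcome section does not, and Hypothesis 3 gives no both-or-either rule, so its error rate is not fixed at 5%

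*Protocol article*

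**What the plan says.** Five places in the protocol article bear on this.

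- **Abstract, Methods:** "Primary outcomes will be 7-day point prevalence and risk reduction at the 6-month follow-up". Two primary outcomes.
- **Effectiveness Outcomes, Smoking Cessation:** "The primary outcome measure will be 7-day point prevalence at the 6-month follow-up". One primary outcome.
- **Effectiveness Outcomes, Risk Reduction:** explains how the change in cigarettes is computed, and calls it neither primary nor secondary.
- **Study hypotheses (Introduction), Hypothesis 3:** predicts that quit rates and risk reduction will both be greater with the recommender system (A+B) than with the standard system (C+D). It gives no rule for the case where only one of them is.
- **Statistical Analyses:** "All analyses will be two-sided, and the alpha error will be set at .05". No order or division of alpha between the two outcomes is stated.

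The word primary also appears in the sample-size text for Hypothesis 1, about the proportion of African American smokers: "for our primary aim, we will need 219 smokers in each group to detect a difference of 10" percentage points.

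**The concern.** A reader who follows the abstract would accept a significant result on either outcome, or perhaps insist on both. A reader who follows the outcome section would look only at 7-day abstinence. These are three different success rules with different error rates, and the article does not choose among them. If abstinence is not significant and risk reduction is, the trial is positive under one reading and negative under the other two.

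A statistical analysis plan that is not shown may add a testing order. It cannot make the abstract and the outcome section agree, and naming the primary outcome is the protocol's own task. Both Results passages say that preliminary analysis is under way, so the point should be settled before the 6-month outcomes are seen by arm.

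**Working it through.** **1. Was alpha divided when the trial was sized?** Inputs are from Sample Size, Hypothesis 3: control quit rate 15%, intervention 24%, two-sided .05, 80% power, 300 per group, Z-test with pooled variance.

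Mean rate = (0.15 + 0.24)/2 = 0.195.

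n per group = [1.960 × √(2 × 0.195 × 0.805) + 0.842 × √(0.15 × 0.85 + 0.24 × 0.76)]² / 0.09²
= [1.098 + 0.469]² / 0.0081 ≈ 303.03, rounded up to 304.

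With 300 per group, power is 79.6%. The stated figure is reproduced at the full .05. At .025 the same calculation needs 368 per group, so no split was used.

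Risk reduction, same section (SD 3, 90% power, 300 per group): (1.960 + 1.282) × 3 × √(2/300) = 0.794, against the stated 0.80. This too is at the full .05.

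**2. False-positive rate for Hypothesis 3 under each reading**, both tests at two-sided .05 and no true effect on either outcome:

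| Reading | Error rate |
|---|---|
| Abstinence is the single primary (outcome section governs) | 5% |
| Both must be significant | at most 5% |
| Either suffices, independent tests | 1 − 0.95² = 9.75% |
| Either suffices, correlation 0.3 | 9.5% |
| Either suffices, correlation 0.5 | 9.1% |
| Either suffices, correlation 0.7 | 8.3% |
| Either suffices, correlation 0.9 | 7.1% |

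The correlated rows come from a simulation of 2,000,000 pairs of normal test statistics. The documents give no correlation, so the range is an assumption. A participant who has quit smokes no cigarettes, so some positive correlation is likely and 9.75% is the less likely end.

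**3. Power if both must be significant.** At the stated 300 per group, with 80% and 90% power, independence gives 0.80 × 0.90 = 72%. But Hypothesis 3 compares A+B with C+D in a trial of 1200 (Study Overview), which is about 600 per arm. There:

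- abstinence, 15% against 24%: power 97.7%;
- risk reduction, 0.80 cigarettes with SD 3: 0.80 / (3 × √(2/600)) = 4.62; 4.62 − 1.96 = 2.66; power 99.6%;
- both: at least 97.7% + 99.6% − 100% = 97.3%, whatever the correlation.

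These figures are before attrition, which the article does not quantify, and they ignore any clustering.

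**The case against.** The strongest reply is that the two statements can be partly reconciled. The sentence naming a single primary outcome stands under a sub-heading that pairs 7-day point prevalence with saliva verification. It may mean only that self-reported abstinence, rather than the NicAlert result, is the primary measure of cessation. Risk reduction then has a parallel heading, in line with the abstract and Hypothesis 3. That is a possible reading. It still leaves two primary outcomes without a both-or-either rule.

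It can also be said that testing order is usually left to the analysis plan, and that .05 per analysis does not exclude a hierarchy. That is true of the order, but not of the conflicting labels.

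Four stronger readings are tempting, and the article does not support them.

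- **Three primary endpoints.** Only two outcomes are ever called primary. The sample-size text speaks of a primary aim within Hypothesis 1, where it can mean the lead aim of the dissemination question. The list of secondary outcomes does not include the African American proportion, so there is no literal clash with that list.
- **An error rate of 14.3% over three tests** (1 − 0.95³). This pools the peer recruitment question with the comparison of messaging systems. They concern different allocated factors, and a separate .05 for each can be defended if declared.
- **Joint power below 80%.** This holds at 300 per group, not at the roughly 600 per arm of the planned comparison.
- **A choice of outcome made after seeing results.** The abstract says 6-month follow-up was still to be completed, and nothing says that the preliminary analysis covers the Hypothesis 3 outcomes.

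**Conclusion.** The point holds in limited form. The article disagrees with itself on whether risk reduction is primary, and Hypothesis 3 lacks a success rule while every test uses an undivided two-sided .05. The correct statement is that the false-positive rate of Hypothesis 3 is not controlled at 5%, rather than that it is inflated. It is 9.75% under an either-suffices rule with independent tests, and about 9.1% to 7.1% at assumed correlations of 0.5 to 0.9. It is at most 5% if both are required or if abstinence alone is primary. Power is not the issue for the planned A+B against C+D comparison, subject to attrition and clustering. The labels should be settled, but the design itself need not change.

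**What to change.** Before the arms are compared on 6-month outcomes, issue a dated clarification:

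1. 7-day point prevalence at 6 months is the single primary outcome of Hypothesis 3, tested at two-sided .05.
2. Risk reduction is tested at two-sided .05 only if the primary result is significant.
3. The abstract, Hypothesis 3 and the two effectiveness outcome sections are reworded to match.
4. Separately, the sample-size text for Hypothesis 1 states that its primary aim means the lead outcome of the dissemination question (H1A), reported as its own claim.

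This keeps the outcome that the abstract and the outcome section share, at the full .05, and adds no participants. The cost is that risk reduction alone can no longer support Hypothesis 3. Because the abstract names it as primary and enrolment is complete, the clarification should say openly that this is a late change of label. A declared rule that both outcomes must succeed would also remove the ambiguity, but an effect on abstinence alone would then not be enough.

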**Results:**

The project is funded from 2017 to 2020 by the Patient Centered Outcomes Research Institute. Enrollment was completed in early 2019, and 6-month follow-ups will be completed by late 2019. Preliminary data analysis is currently underway.

**Conclusions:**

Conducting a hybrid study with both effectiveness and dissemination hypotheses raises some unique challenges in the study design and analysis. Our study addresses these challenges to test new innovations and increase the effectiveness and reach of DISCs.

**International Registered Report Identifier (IRRID):**

DERR1-10.2196/14814

## Introduction

Smoking continues to be a public health concern and is the leading cause of preventable death in the United States [1]. Annually, over 6 million deaths in the world are attributable to smoking, including 480,000 in the United States [1]. Although the overall rates of smoking have reduced, the rates among socioeconomically disadvantaged subgroups are considerably higher [2]. In particular, African American smokers suffer disproportionately due to smoking-related diseases including several cancers, cardiovascular disease, and cerebrovascular disease [2-4]. Although they smoke fewer cigarettes and start smoking at an older age, these smokers are more likely to die from smoking-related diseases than white smokers [1]. Identifying strategies to increase reach and effectiveness of tobacco cessation programs, especially among vulnerable populations, is an ongoing research challenge [5].

Digital Interventions for Smoking Cessation (DISCs) are health communication programs readily accessible via the internet and smartphones. DISCs can include a number of functions designed to support a smoker’s cessation attempt. Previous research has shown that DISCs can be effective. In our prior trial, our DISC—Decide2Quit [6]—achieved a cessation rate of 30% at 6 months, which is much higher than the 7% rate at which smokers quit without support [7]. DISCs have the potential to reach a large and diverse group of smokers. Access to DISCs has previously been limited for many smokers because of the disparities in internet access. However, the digital divide in internet access has decreased considerably with increased broadband availability and smartphone use [8,9]. Despite this increased access and potential for effectiveness, the impact of DISCs has been limited. New ways to increase the access and effectiveness of DISCs are needed.

In response to a Patient Centered Outcomes Research Institute (PCORI) call for communication and dissemination research, we proposed a dissemination study—Smoker-to-Smoker (S2S)—to test whether providing access to a peer recruitment toolset that facilitates recruitment of friends and family members to the intervention will increase recruitment rate and increase variability of the sample. Because of feedback from PCORI and peer review, we expanded our study to also test the effectiveness of a machine learning–based approach (recommender system) for computer-tailored health communication (CTHC). Thus, our project is a hybrid effectiveness dissemination trial including both effectiveness and dissemination hypotheses (Textbox 1). Conducting a hybrid study with both effectiveness and dissemination hypotheses raises some unique challenges in the design and analysis of our study. Our paper describes the intervention functions and the study protocol we developed to address previously mentioned challenges. We also describe the budget impact analysis we will use to assess the cost of implementing this intervention.

Study hypotheses.Hypothesis 1: DisseminationH1A: Peer recruitment will recruit a greater proportion of African American smokers compared to standard online recruitment.H1B: Peer recruitment will reduce recruitment time (time to recruit each participant) compared to standard online recruitment.Hypothesis 2: Repeated use of Decide2Quit functionsH2A: Repeated use among those exposed to the fully enhanced group (access to peer recruitment toolset and recommender CTHC) will be greater than repeated use among those exposed to (1) peer recruitment toolset only, (2) recommender CTHC with no peer recruitment toolset, and (3) standard group (no peer recruitment toolset and standard CTHC).H2B: Repeated use among those exposed to the peer recruitment toolset will be greater than repeated use among those exposed to the standard group.H2C: Repeated use among those exposed to the recommender CTHC will be greater than repeated use among those exposed to the standard group.Hypothesis 3: EffectivenessQuit rates and risk reduction among participants exposed to the recommender CTHC (A+B) will be greater than those among participants exposed to the standard group (C+D).

## Methods

### Study Overview

The goal of this study (ClinicalTrials.gov: NCT03224520) is to recruit 1200 smokers to test our effectiveness and dissemination hypotheses. To participate in the study, all smokers will register online for the Decide2Quit DISC. Randomization will occur after registration using a multilevel approach, as detailed below. We will follow smokers for 6 months from their registration date. Following a description of the intervention and comparison, our protocol is described in detail below. The protocol of our study was approved by the Institutional Review Board at the University of Massachusetts Medical School.

### The Smoker-to-Smoker Functions

#### The Computer-Tailored Health Communication System

CTHC is a frequently used tool in behavioral science and is focused on the selection of appropriate messages for an individual. CTHC increases personal relevance of health messaging by matching the messages to an individual’s or group’s characteristics [10]. CTHC can be effective in motivating behavior change [11-17]. Standard CTHC has traditionally been accomplished using rule-based approaches in which selected variables from patients’ baseline profile are matched to specific if-then tailoring rules to send tailored messages to specific subsets of patients [10,18]. As an alternative to rule-based approaches, companies such as Amazon use machine learning algorithms (ie, recommender systems) to tailor content. These recommender systems have several advantages over rule-based approaches, including the ability to continuously learn from user feedback (eg, liked product and products purchased) and enhance personal relevance. Textbox 2 provides an example of how a standard and recommender CTHC may differ in DISCs [18]. In our prior pilot randomized controlled trial (RCT) [19], we developed a recommender CTHC and compared this system with a standard CTHC system that showed effectiveness. The recommender system significantly outperformed the rule-based system on the number of days (out of 30) in which message relevance influenced smokers to quit. In the recommender system smokers, 74% strongly agreed or agreed that the messages influenced them to quit smoking, while this was only reported by 45% in the standard group (*P*<.01) [20]. Among those who completed follow-up, 36% (20/55) of the recommender system smokers and 32% (11/34) of the rule-based system smokers stopped smoking for one day or more (*P*=.70). Our goal in the S2S study is to rigorously test the recommender system against the standard CTHC for smoking cessation over a 6-month period. The primary difference between the recommender CTHC and standard CTHC will be the way in which messages are selected for the participant. Since our goal is to test the selection method, both systems will select from the same database of messages. We will first describe the motivational message database used in the study followed by the standard CTHC selection system and the recommender CTHC system.

Computer health-tailored communication (CHTC). An example of a standard CHTC versus a recommender CHTC [
17].John Smith, a 38-year-old smoker, has been smoking for 15 years. He has made multiple quit attempts in the past, but during each attempt, he gained between 10 and 20 pounds. Currently, fear of weight gain is a significant barrier to another quit attempt.John is trying to quit again and registers on Decide2Quit. For 8 weeks, the system sends two tailored emails per week to John Smith to help him quit.**Standard CTHC**In this approach, tailoring is based on information that John provides when he registers. For this example, we focus on one characteristic only: gender.Since women are typically more concerned about weight gain after quitting [21,22], experts have specified that half of the emails sent to women should contain information related to weight gain, but only one quarter of the emails sent to men should be focused on weight gain. After registering on Decide2Quit, John receives the first email that targets weight gain support in the second week (third message) of the intervention. John likes the message and finds the tips it offers useful. He looks forward to receiving similar messages. However, the next five messages he receives focus on other topics. The next weight gain message arrives only on week 5.John does not think the system helped and fails in his attempt to quit.**Recommender CTHC**In this approach, the selection of the message is based on the collective intelligence data, not on preset rules.  After registering on Decide2Quit, John visits the weight gain support page on the website (implicit data). The system uses these data and selects one of the messages targeting weight gain and sends it to John on week 2 (third message). John likes the messages and rates the message highly (explicit data). The system then notes both items of implicit and explicit feedback and regularly sends messages targeting weight gain to John. The system also repeats the message that John rates highly.Because the intervention targeted his needs more specifically, John finds these messages useful and succeeds in his attempt to quit.We have provided a simple example for ease of understanding. We have not included in this example how the group’s feedback can help John.

